## Concomitant care

As the present trial focusses on feasibility rather than efficacy, participants are allowed to receive other parallel treatments for their ED. Concurrent use of psychoactive medications is allowed in the trial, with type and dosage of medication assessed, with the exception of neuroleptic or benzodiazepine intake.

### Outcomes

Table 1 gives an overview on assessment points and outcome measures.

#### Primary outcome measure

We chose BE frequency in the last four weeks according to the *Eating*
*Disorder*
*Examination*
*(EDE)* [48] as a primary clinical outcome. We compare changes in BE episodes at the four weeks follow-up (T8) to baseline (T0). BE frequency is of high clinical relevance as BE constitutes the core psychopathology of BED [40]. Moreover, most efficacy trials investigating psychotherapy as treatment approach look at BE frequency as primary outcome [3, 5].

#### Secondary outcome measures

Secondary outcomes will be assessed based on validated structured clinical interviews, validated self-report instruments as well as established neuropsychological tasks. The clinical BED diagnosis as well as comorbid mental disorders are assessed according to the current gold standard [42] which are standardized structured expert interviews, which are applied by trained raters. The respective assessment points can be seen in Table 1.

*Eating disorder pathology including BE frequency* as well as diagnostic criteria of BED will be assessed using the *Eating Disorder Examination*
*(EDE)* [48]. Proportion of (partial) remission will be assessed according to the EDE diagnostic criteria for BED. Further, a self-developed protocol assessing BE frequency in the last seven days to assess short-term changes will be assessed [49].

*General psychopathology* will be assessed using the *Structured Clinical Interview for DSM-5 (SCID-5-CV)* to assess current and lifetime DSM-5 Axis I diagnoses of mental disorders [50]. The Beck’s Depression Inventory, Version 2 (BDI II), is used to assess depressive symptoms.

*Eating behaviour* will be assessed using the Three-factor Eating Questionnaire (TFEQ) including impulsive eating and food craving with the Food Craving Questionnaire, State Version (FCQ-S).

*Body Mass Index (BMI)* will be calculated based on objectively assessed body weight and height at T0 and T8 and assessed as self-report at T9.

*Quality of life* is assessed based on the WHO (Five)—Well-being Questionnaire (WHO-5).

*Impulsivity and Inhibitory control* will be assessed based on different approaches: On a behavior level, performance measures of the food-related antisaccade task will be analyzed, including error rate and latency [37, 38] as assessed by eye tracking (see above). Additionally, task performance in another general well-established inhibitory control task, the Go/No-Go task, will be assessed. Again, error rate and latency will be analyzed in order to estimate inhibitory control independent of disorder-relevant stimuli. Additionally, the Go/No-Go task has recently been shown to be sensitive towards changes in impulsivity in patients receiving a psychotherapy treatment [51]. Additionally, we will assess different components of self-reported impulsivity, i.e. negative urgency with the "UPPS Impulsive Behavior Scale" (UPPS), trait impulsivity with the Barratt Impulsiveness Scale (BIS-15) and common impulsive behaviours in the past seven days with a self-developed protocol [49].

*Rating of stimulus valence* of the presented food pictures is assessed based on visual analogue scales (–5 to 5) concerning valence (“very unpleasant” to “very pleasant”), appetite (“very unappetizing” to “very appetizing”), wanting (“not at all” to “very much”) and liking (“not at all” to “very much”).

*Acceptance and feasibility* will be estimated based on the percentage of included patients from the eligible patients at T0 as well as based on the drop-out rate throughout T0 to T9.

*Treatment evaluation* will be assessed using a self-developed self-report evaluation sheet which will cover aspects such as subjective need and motivation for training uptake, feasibility and acceptability of the treatment as well as overall satisfaction.

### Participant timeline

The individual participant timeline is depicted in Fig. 1.

Study duration for each patient comprises 14 weeks. This includes two weeks of training and a post-intervention follow-up period of three months. Table 1 shows the nine assessment time points during the study (T0–T9), while T0 is the baseline assessment, there is an assessment at each training session (T1–T6), a post-intervention assessment (T7) within the two weeks after training termination, a second post-intervention assessment four weeks after training termination (T8) and a three-months follow-up assessment focusing on changes in ED symptoms conducted via telephone (T9).

### Sample size

The present trial is a clinical pilot study that aims at the investigation of feasibility and effect sizes rather than significant group differences in order to establish a data basis for the preparation of a larger efficacy trial. Therefore and also due to the very limited prior evidence in the field [15, 17], a sample size calculation was not conducted.

### Randomization

Eligible patients will be randomized 1:1 between the verum stimulation and the sham stimulation. Randomization takes place after completion of the baseline assessment (T0) and is performed independently via a code system established by the Institute for Clinical Epidemiology and Applied Biostatistics, Tübingen, Germany (IKEAB). Block randomization with variable block lengths will be used.

### Blinding

ACCElect is performed as a double-blind trial. The participants as well as the data assessors are blinded regarding the treatment group. This is implemented by using a unique 5-digit code for each participant which activates either verum or sham stimulation. Moreover, also in the sham condition, tDCS electrodes are properly mounted and current is applied for 43 s at the beginning of each training session, while during this time, no inhibitory control training is conducted. Therefore, participants allocated to the sham condition perceive typical sensations of tDCS (e.g. tingling) which is considered as a valid placebo condition. To assess if blinding was successful, participants will be asked to guess in which condition they have been randomized and to indicate how certain they feel about this.

### Data management

All data is assessed pseudonymized. Data will predominantly be entered manually by either the study personnel or patients themselves for self-report measures. Data from paper-based source data will later be transferred to an electronic study database and fidelity and plausibility to the source data will be checked at random by the study personnel. All trial data will be stored in line with the European General Data Protection Regulation 2018.

### Statistical methods

The primary analysis will use the number of BE episodes in a Poisson regression model with baseline adjustment. In secondary analyses, a mixed model approach will be used to analyze the primary outcome (PO) and secondary outcomes (SOs) also with baseline adjustment. Effect sizes will be analyzed and reported for PO and SOs. From the Poisson regression, relative risks will be reported. For binary outcomes, odds ratios and for quantitative outcomes standardized differences will be reported. Primary parameters will be time vs. treatment interactions at several time points after baseline. P-values will be reported but have to be interpreted non confirmatorily. Planned, non-confirmatory subgroup analyses will be done separately for male and female subjects. The same will be done for patients receiving concomitant care vs. patients receiving no concomitant care. There will be no interim analysis. The primary analysis will be done in the intent to treat population, which is defined by including all patients with baseline assessment. Multiple imputation will be used for subjects dropping out according to the method of Rubin. The imputation model will use 500 replications and will include age, gender and baseline assessment. Furthermore, available values from preceding visits will be included. Analyses will be performed using SPSS for Windows and R.

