**Methods:**

ACCElect is a prospective, randomized controlled pilot trial investigating a novel, food-related inhibitory control training combined with transcranial direct current stimulation (tDCS). 40 patients with BED will be randomly assigned to receive the training either combined with verum or with sham stimulation (control condition). The inhibitory control training is based on principles of the antisaccade paradigm and comprises six training sessions over two weeks. Core aims are the investigation of feasibility and clinically relevant effects of a tDCS-enhanced inhibitory control training in BED patients and the establishment of a data basis for a larger efficacy trial. The primary clinical endpoint is binge-eating (BE) frequency in terms of changes in BE episodes four weeks after treatment termination as compared to baseline. Key secondary outcomes comprise ED pathology and general psychopathology, inhibitory control capacities, quality of life as well as acceptability and satisfaction with the intervention.

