### Existing knowledge

Recently, NIBS has been used to influence eating behaviour and has been probed in the treatment of eating and weight disorders, while most studies have used tDCS as a technique [15, 17, 19]. Evidence in healthy and sub-clinical groups as well as in people affected by obesity suggests that tDCS and other forms of NIBS can reduce (short-term) food cravings [15], however, studies investigating the potential of NIBS in clinical populations are still very scarce and have mostly focused on patients with anorexia nervosa (AN) [15]. There is to the best of our knowledge only one published study which has probed the use of tDCS in a sample of people affected by BED or sub-clinical BED [20]. In this study, 30 individuals with BED received either a verum or sham stimulation of the right dlPFC with 2 mA [20], and the verum stimulation resulted in reduced short-term food craving and urge to binge-eat in male participants only and in overall reduced caloric intake directly after the stimulation. Of note, this study exclusively used tDCS as an intervention and did not pre-define a primary outcome or planned subgroup analyses.

However, it has to be considered, that tDCS itself does not induce neuronal activity like e.g. transcranial magnetic stimulation and its effects therefore critically depend on concurrent brain activity [21, 22]. This property of tDCS thus allows for targeting specific networks and associated cognitive or behavioral functions [23–25]. Therefore, a targeted combination with training has been put forward as a promising approach to support adaptive plasticity underlying the therapeutic effects of tDCS [16, 26, 27]. Therefore, combinations of tDCS and cognitive training approaches are discussed as a promising new treatment approach [16]. Particularly, tDCS administration to the prefrontal cortex during task training has shown some promising effects in patients with depressive disorder [28–30] and schizophrenia [16, 31]. BED is also associated with dysfunctions in prefrontal brain areas [14] and patients with BED have demonstrated impairments in a range of cognitive tasks, predominantly in the domain of inhibitory control [9]. These tasks can also be used in terms of training tools to enhance cognitive control [19].

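### Exploratory subgroups are analysed separately by sex and by concomitant care with no treatment-by-subgroup interaction named, so the results cannot show whether the effect differs between subgroups (minor)

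*Protocol article*

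**What the plan says.** Under Statistical methods the article fixes the subgroup method: "Planned, non-confirmatory subgroup analyses will be done separately for male and female subjects". The next sentence extends it: "The same will be done for patients receiving concomitant care vs. patients receiving no concomitant care". The interactions named in that section concern time, not subgroups: "Primary parameters will be time vs. treatment interactions at several time points after baseline". The section also limits the claims that may be made: "P-values will be reported but have to be interpreted non confirmatorily".

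The abstract sets the size: "40 patients with BED will be randomly assigned to receive the training either combined with verum or with sham stimulation". Under Randomization, allocation is 1:1 and "Block randomization with variable block lengths will be used"; strata are not mentioned. The Sample size section says that no calculation was done, because the pilot is meant to yield feasibility data and effect sizes for a larger trial.

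Under Existing knowledge the article describes an earlier tDCS study in BED that found "reduced short-term food craving and urge to binge-eat in male participants only". It remarks that this study had prespecified neither a primary outcome nor its subgroups.

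**The concern.** A subgroup split is normally read as an answer to one question: does the effect differ between the groups? Two separate models do not address it. Each tests whether the effect in its own stratum is zero. When one stratum gives a small p-value and the other does not, the contrast mostly reflects stratum size and chance. It is neither an estimate nor a test of effect modification.

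The pilot's effect sizes are meant to feed a larger multicentre trial. An apparent effect in one sex only, or only in patients without other treatment, could influence eligibility or stratification there although it is noise. Prespecifying the subgroups, as this plan does, guards against selective reporting. It does not make a comparison of two stratum results valid.

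**Working it through.** The plan gives no subgroup size, effect size, alpha or power, so there is no figure of its own to reproduce.

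**Inputs from the article:** N = 40; 1:1 allocation, hence 20 per arm.

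**Assumptions (not in the article):** two-sided 0.05; outcome standardised to SD 1; each sex split evenly across arms except in step 4; no dropout; male share 10% to 50% (4 to 20 men); normal approximation for power.

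**1. Standard errors.** Within a sex: SE = sqrt(4/n_sex). Treatment-by-sex interaction: SE = sqrt(4/n_men + 4/n_women).

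**2. How often separate tests disagree when the true effect is identical.** With power P_m in men and P_w in women, the chance that exactly one is significant is P_m(1 − P_w) + P_w(1 − P_m).

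- 6 men, 34 women, effect 0.8 SD: SE = 0.816 and 0.343; power 0.164 and 0.645; 0.164 × 0.355 + 0.645 × 0.836 = 0.60.
- 20 and 20: power 0.432 in each; 2 × 0.432 × 0.568 = 0.49.
- With a common effect of 0.5 SD the range over 6 to 20 men is 32% to 34%; with 1.0 SD it is 48% to 68%.
- With no effect in either sex it is 2 × 0.05 × 0.95 = 9.5%.

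The disagreement persists with an even sex split, so it does not depend on men being few.

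**3. Precision.** 95% CI half-widths in SD units, using t quantiles with n_sex − 3 degrees of freedom within a sex and 35 for the interaction. For reference, the whole trial with 20 per arm gives 0.64 SD (t with 38 degrees of freedom).

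| Men / women | Men only | Women only | Interaction | Interaction power for a 0.8 SD difference |
|---|---|---|---|---|
| 4 / 36 | 12.7 | 0.68 | 2.14 | 11% |
| 6 / 34 | 2.60 | 0.70 | 1.80 | 14% |
| 8 / 32 | 1.82 | 0.72 | 1.60 | 17% |
| 12 / 28 | 1.31 | 0.78 | 1.40 | 21% |
| 20 / 20 | 0.94 | 0.94 | 1.28 | 24% |

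**4. Balance within sex.** If allocation is not stratified by sex, the number of men per arm is hypergeometric. The chance that an arm holds fewer than 2 men is 60% with 4 men, 18% with 6, 4% with 8 and under 1% with 10 or more.

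**5. Count scale, illustration only.** Assume means of 8 and 5.6 episodes (rate ratio 0.7) and dispersion k = 0.5. Then SE(log RR) = sqrt((1/8 + 1/5.6 + 2 × 0.5)/n per arm).

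- 3 men per arm: SE 0.659, CI factor exp(1.96 × 0.659) = 3.6 either way.
- 17 women per arm: SE 0.277, factor 1.7.
- Ratio of the two rate ratios: SE sqrt(0.659² + 0.277²) = 0.715, factor 4.1.

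**The case against.** The strongest reply is that the plan promises nothing it cannot deliver. It calls the subgroups non-confirmatory, extends that caution to all p-values, and aims at effect sizes in a pilot. It nowhere says that results will be compared between sexes or that a sex difference will be tested. A reader might infer that the plan sets out to repeat the men-only conclusion of the earlier study. The article gives no reason for the sex split and criticises that study for lacking planned subgroups, so that reading is unsupported. What stands is narrower: the stated method yields two results side by side, and the non-confirmatory label does not turn their contrast into an estimate of a difference.

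A reader might also infer that results in men will be close to inestimable. The article gives no expected number of men. That description fits about 4 to 6 men; with 8 to 12 the estimate is very imprecise, and with an even split it is estimable (0.94 SD). Nor can one say that randomisation is unbalanced within sex. The article is silent on strata, so step 4 is conditional.

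It is also fair to say that the interaction is imprecise, and on the count scale even less precise than the estimate in men (factor 4.1 against 3.6). That is true, but its wide interval shows the uncertainty about the difference, which two separate results conceal.

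Finally, an analysis plan that is not shown may add an interaction. The point therefore concerns the method the article states, not an omission.

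**Conclusion.** The point holds as a minor one. The article fixes separate analyses for both subgroup factors, and such analyses cannot show whether the effect differs between strata. Under an identical 0.8 SD effect, exactly one sex would be significant in roughly 49% to 60% of trials with 6 to 20 men. The figure is lower for smaller common effects (32% to 34% at 0.5 SD). It rests on a two-sided 0.05 level, equal splits within sex, no dropout and a normal approximation. The same logic applies to concomitant care, for which the article gives no expected split either.

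How imprecise the within-sex estimates will be depends on the assumed male share; very imprecise or possibly inestimable applies only if about 4 to 6 men enrol. The primary analysis is untouched, and the harm is confined to misreading exploratory results.

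**What to change.** For each subgroup factor (sex; concomitant care as recorded at T0), fit one model on all randomised patients with a treatment-by-subgroup term. Report the ratio of rate ratios for the count outcome, or the difference in effects for quantitative outcomes, with its 95% CI. Using T0 status keeps care started after randomisation out of the subgroup definition. Include the same interaction in the imputation model, so that imputation does not pull the subgroup effects together. Show subgroup estimates descriptively with the number of patients per arm, and state that no subgroup-specific effect will be concluded from separate stratum p-values.

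The cost is a few sentences and a little more analysis work. In the mixed model with time-by-treatment terms, the subgroup contrast becomes a three-way term, so it is slightly more than one extra coefficient there. The interaction estimate will be visibly imprecise: power for a 0.8 SD difference is about 11% to 24% across the assumed sex splits. The change makes the inference valid; it cannot make 40 patients informative about subgroups.

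### The stated imputation model omits treatment arm, so the estimated tDCS effect is pulled toward no effect, by up to about the drop-out proportion and by less where earlier post-baseline counts exist

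*Protocol article*

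**What the plan says.** All the relevant text is in the Statistical methods section of the protocol article.

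- Primary model: "The primary analysis will use the number of BE episodes in a Poisson regression model with baseline adjustment".
- Parameters of interest: "Primary parameters will be time vs. treatment interactions at several time points after baseline". Treatment is therefore in the analysis model.
- Population: "The primary analysis will be done in the intent to treat population, which is defined by including all patients with baseline assessment". A patient who leaves early still counts in the primary result.
- Missing data: "Multiple imputation will be used for subjects dropping out according to the method of Rubin".
- Imputation predictors: "The imputation model will use 500 replications and will include age, gender and baseline assessment". The next sentence adds: "Furthermore, available values from preceding visits will be included".

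Neither predictor sentence names the randomised arm, and imputation within arm is not mentioned. The Primary outcome measure section sets the comparison at the four-week follow-up (T8) against baseline (T0). Study aims and Sample size make effect sizes, rather than significance tests, the purpose of the pilot, with a later multicentre trial to be sized from them.

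**The concern.** An imputation model should contain every term of the analysis that follows it. Here the analysis estimates a treatment effect and the stated imputation model has no treatment term.

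A patient who leaves before giving any post-baseline binge-eating value is imputed from age, gender and baseline alone, that is, from a distribution pooled over verum and sham. A patient who leaves later is imputed partly from earlier counts, which reflect the arm only as far as they predict T8. If tDCS has an effect, both cases move the two arms closer together. This does not need informative or unequal drop-out. The number of imputations does not help either: 500 replications reduce Monte Carlo noise and leave this bias untouched.

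The quantity that shrinks is the pilot's main product, the effect size for planning the next trial.

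**Working it through.** The article states no power, assumed effect or drop-out rate, so there is no figure of its own to reproduce. The size of the bias was checked in two ways.

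**Inputs from the article:** 40 patients, 1:1 allocation, baseline-adjusted Poisson regression, and the imputation predictors listed above.

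**Assumed inputs, not in the article:** true rate ratio 0.60; mean counts of about 16 at baseline and 12 under sham at T7 (end of treatment) and T8; drop-out 10%, 20% or 30%, completely at random; the same arm effect at T7 as at T8.

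**1. Arithmetic.** Let d be the drop-out share and k the share of the arm effect that earlier values carry into the imputation. The share of the difference in means that is retained is 1 − d(1 − k).

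- k = 0 (no post-baseline values): 0.90, 0.80 and 0.70 at d = 0.10, 0.20 and 0.30.
- k = 0.5: 0.95, 0.90 and 0.85.

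For the rate ratio at d = 0.20, the T8 means are 12 under sham and 12 × 0.60 = 7.2 under verum, and the pooled mean is 9.6.

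- k = 0: (0.8 × 7.2 + 0.2 × 9.6) / (0.8 × 12 + 0.2 × 9.6) = 7.68 / 11.52 = 0.667.
- k = 0.5 (drop-outs imputed at 8.4 under verum and 10.8 under sham): (5.76 + 1.68) / (9.60 + 2.16) = 7.44 / 11.76 = 0.633.

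**2. Simulation.** Counts were Poisson with between-patient variation. Missing T8 values were imputed by normal regression on log counts and then analysed by Poisson regression on arm and log baseline. Predictors were age, gender and baseline, with or without a T7 count and with or without arm. In the T7 case, every T8 drop-out had T7 observed, with a T7–T8 residual correlation of 0.3 to 0.7. Share of the log rate ratio retained, with estimated rate ratio (RR), at n = 400 to limit noise:

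| Drop-out | No arm, baseline predictors only | No arm, T7 count available | Arm included |
|---|---|---|---|
| 10% | 88–89% (RR about 0.64) | 94–95% (about 0.62) | 99–100% |
| 20% | 78% (about 0.67) | 86–89% (0.63–0.65) | 99–103% |
| 30% | 66–68% (about 0.71) | 79–84% (0.65–0.67) | 100–101% |

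At the planned 40 patients, 20% drop-out and correlation 0.5, the full-data rate ratio was 0.591. Without arm it was 0.668 with baseline predictors only (ln 0.668 / ln 0.591 = 0.77) and 0.627 with T7 (ln 0.627 / ln 0.591 = 0.89). With arm it was 0.587 in both cases.

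With baseline predictors only, the loss on the log scale is 11–12%, 22% and 32–34%. It is therefore about the drop-out share, marginally above it, and not a strict ceiling. With T7 observed, roughly half remains.

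**Consequence for planning.** Required sample size varies as 1/effect². If the next trial were sized on the attenuated estimate, other inputs equal, the factor would be 1/0.89² = 1.26 to 1/0.77² = 1.69.

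**The case against.** The strongest reply is that the predictor list is not called exhaustive. The article says what the model will include, does not say that nothing else enters, and does not rule out imputing by arm. It is a condensed article, and full imputation detail usually sits in an analysis plan. This lowers certainty about intent: the sponsor may well mean to include arm. It does not remove the point, because the article goes as far as fixing the predictors and the number of replications, and the variable left out is the one being estimated.

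A reader might also infer that imputed T8 counts ignore the arm altogether and that the loss always equals the drop-out share. The documents do not support that. Values from preceding visits are explicitly added, and they carry part of the arm effect. Full attenuation applies only to patients with no post-baseline binge-eating data. How many earlier counts exist cannot be checked, because Table 1 is not shown.

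The error is also conservative and the trial small. It does not create a false claim of benefit, p-values are to be read as non-confirmatory, and at 40 patients sampling error may well exceed the bias. All of this stands. It limits the urgency, but a systematic shrinkage of the effect size is still unwelcome in a pilot run to estimate it.

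Three further inferences go beyond the text. A distorted pooled standard error was not shown for the planned Poisson model. That T9 values would be wrongly discarded does not follow, since the text addresses patients who drop out, and these would normally have no T9. Nothing shows that concomitant care or a particular imputation distribution is needed.

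**Conclusion.** The point holds in this form: the imputation model, as stated, omits treatment arm, and following it would bias the primary estimate toward no effect whenever a true effect exists and some T8 values are missing. At an assumed 20% drop-out and a true rate ratio near 0.60, about 77–89% of the log rate ratio is retained, an estimated rate ratio of about 0.63–0.67. The lower retention applies if drop-outs have only baseline data, the higher if all of them have a T7 count.

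The direction follows from the stated model. The size rests on assumed drop-out, correlation and effect, none of which the article gives. If drop-out is very low the bias is negligible. If the effect is weaker at T7 than at T8, the T7 count carries less of it and the loss moves toward the larger figure.

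**What to change.** State that treatment arm is a predictor in the imputation model, or that imputation is done separately by arm. Keep age, gender, baseline, preceding-visit values and the 500 imputations. With 20 patients per arm under 1:1 allocation, adding arm as a covariate is the lighter option, because imputing by arm leaves fewer patients for each imputation model.

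The cost is one phrase of plan wording and one more variable in the imputation, with no extra data. If arm was always intended, the sentence only records it. The change should be dated before the allocation is unblinded.

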A further challenge applying to the whole rapidly evolving research area is very limited evidence on which cognitive training approach might work best in terms of sustainable and clinically relevant changes in ED pathology. As outlined above, most previous evidence on the combination of NIBS with cognitive tasks stems from healthy convenience samples or subclinical groups [16, 18], and in the ED field, most studies have used stimulation only approaches [15, 17]. There are multiple well-validated and widely used neuropsychological paradigms to assess prefrontal brain functioning in terms of inhibitory control capacities, including the SST and GoNoGo tasks, but also the antisaccade paradigm. A currently ongoing study uses an approach bias modification training in combination with tDCS [32] as this has previously shown promise in patients with EDs. A recent meta-analysis found significant effects of tDCS on inhibitory control as assessed by the SST in healthy and in clinical samples, but not on GoNoGo performance [18]. It is also important to consider that the most widely used tasks also tap on slightly different sub-components of inhibition, for instance, the SST measures the ability to interrupt an already initiated behavior, while the GoNoGo and antisaccade paradigm assess the ability to suppress a prepotent response. These slight differences might have rather significant consequences when translating into clinical outcomes regarding targeted disorder symptoms as well as for the interplay with stimulation effects which are intended to augment the training effects [16]. Additionally, there is also the potential of delayed effects of tDCS on task performance [54], rendering it interesting for future pilot and efficacy trials to include cognitive task performance also within follow-up assessments. We aim to contribute to this evidence with our trial as more research is needed on which performance aspects are best targeted with the training as well as which aspects can be best augmented using tDCS. Therefore, we are also reporting on GoNoGo performance of our trial participants as secondary outcome.

Our main focus of the 12-week follow-up assessment are potential changes in the central clinical outcomes of the trial, while ensuring low attrition by a concise assessment. However, this was on the expense of other variables, and it would, for instance, be also insightful to have QoL data at follow-up.

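### For a missing T8 primary outcome, the imputation model names only backward-looking predictors, so values from the T9 telephone assessment are not among them

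*Protocol article*

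**What the plan says.** All points are in the protocol article.

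- **Outcome** (Primary outcome measure): "We chose BE frequency in the last four weeks according to the" Eating Disorder Examination (EDE) interview. The comparison is T8, four weeks after training, with baseline (T0).
- **Missing data** (Statistical methods): the primary analysis includes everyone with a baseline assessment. "Multiple imputation will be used for subjects dropping out according to the method of Rubin". The model has 500 replications and uses age, gender and baseline. The list ends: "Furthermore, available values from preceding visits will be included".
- **T9** (Participant timeline): "a three-months follow-up assessment focusing on changes in ED symptoms conducted via telephone (T9"). The Discussion adds: "Our main focus of the 12-week follow-up assessment are potential changes in the central clinical outcomes of the trial".
- **Mode of the visits** (Secondary outcome measures): body mass index rests on "objectively assessed body weight and height at T0 and T8 and assessed as self-report at T9". The measured weight suggests that T8 is held on site.
- **Status** (Sample size; Statistical methods): a pilot without a sample size calculation, whose p-values are not confirmatory.

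**The concern.** The article does not leave the imputation model open. It fixes the predictors, and those named all precede the value to be imputed. T8 seems to need attendance, whereas T9 needs only a telephone call. The Discussion says that the pandemic affects trial conduct, especially under lockdowns, and that T9 was kept short to limit attrition. A patient who misses T8 and answers at T9 is therefore foreseeable. For that patient, a later observation of the same symptoms exists and is not named.

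At stake is how well the T8 count is filled in. With 40 patients randomised 1:1, each missing T8 is 1/20 = 5% of an arm. The trial is meant to supply effect sizes for planning a larger one.

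**Working it through.** The plan gives no drop-out rate, variance or correlation, so none of its figures can be reproduced. What follows rests on assumptions.

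**1. Order of visits.** T8 is four weeks after training and T9 about twelve. T9 is thus not a preceding visit for T8. With a four-week recall, T8 covers roughly weeks 0-4 after training, and a T9 count would cover roughly weeks 8-12. The windows do not overlap, so T9 can help to predict T8 but cannot replace it.

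**2. Explained variance of a missing T8.** Assumed correlations: T0-T7 0.6, T0-T8 0.5, T7-T8 0.6, T0-T9 0.4, T7-T9 0.5. The T8-T9 correlation r varies. It is also assumed that T7 and T9 each yield a binge count (Table 1 is not shown).

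From T0 and T7:
R² = (0.5² + 0.6² − 2·0.5·0.6·0.6) / (1 − 0.6²) = 0.25/0.64 = 0.39.

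Adding T9. Regressing T9 on T0 and T7 gives coefficients (0.4 − 0.6·0.5)/0.64 = 0.156 and (0.5 − 0.6·0.4)/0.64 = 0.406. Hence:
- residual variance of T9 = 1 − (0.4·0.156 + 0.5·0.406) = 0.734
- residual covariance with T8 = r − (0.5·0.156 + 0.6·0.406) = r − 0.322
- gain in R² = (r − 0.322)² / 0.734

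Without a T7 value, R² from T0 alone is 0.5² = 0.25. With T9 it is (0.25 + r² − 0.4r)/(1 − 0.4²).

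| r (T8-T9) | T0+T7 | T0+T7+T9 | T0 | T0+T9 |
|---|---|---|---|---|
| 0.4 | 39% | 40% | 25% | 30% |
| 0.5 | 39% | 43% | 25% | 36% |
| 0.6 | 39% | 50% | 25% | 44% |
| 0.7 | 39% | 59% | 25% | 55% |
| 0.8 | 39% | 70% | 25% | 68% |

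The residual SD of an imputed T8 is √(1 − R²). With T7 it is 0.78 SD, falling to 0.75 at r = 0.5 and 0.55 at r = 0.8.

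**3. Effect on the treatment contrast.** A simulation of 400,000 records used standardised log binge scores and single regression imputation, so it shows bias and not sampling error. Assumptions: true arm effect −0.50 SD; correlations T0-T7 0.5, T0-T8 0.45, T0-T9 0.4, T7-T8 0.65, T7-T9 0.55, T8-T9 0.70; T7 known for half of those missing T8. To isolate T9, both models below include treatment arm.

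- **Missingness unrelated to outcome:** adding T9 changes the contrast by at most 0.001 SD. Leaving T9 out causes no bias.
- **Missingness rising with the unseen T8 value** (log-odds 1 per SD; 20% missing; T9 known for half of these): the contrast goes from −0.466 to −0.472, and the mean error of the imputed values from 0.60 to 0.50 SD too low.
- **Same mechanism, 10-30% missing, T9 known for 25-90%:** the contrast shifts by 0.002 to 0.014 SD. With T9 the imputed values are still 0.42 to 0.57 SD too low.

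Arm is not among the predictors that the article lists. If it were really left out, T9 would partly stand in for it and move the contrast more (−0.400 to −0.427 in the 20% setting). That shift reflects the missing arm term, which is a separate matter.

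**The case against.** Several objections stand, and they limit the point.

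- **The text excludes nothing.** A reader might infer that T9 values are thrown away. The article lists what goes in and does not say that nothing else may. Its rule is for patients who drop out, and someone who answers at T9 has not clearly done so. Someone who truly leaves before T8 has no T9 value to lose.
- **A T9 binge count is implied, not shown.** T9 covers eating disorder symptoms and the central clinical outcomes, but the schedule table is not visible.
- **T9 has another route in.** A secondary mixed model analyses the primary outcome at several time points. If T9 is one of them, that model uses it.
- **T9 need not be the best predictor.** It lies about eight weeks from T8, further away than T7. If its correlation with T8 is only 0.4 or 0.5, explained variance rises from 39% to just 40% or 43%.
- **A bias favouring verum does not follow.** If 4/20 verum and 1/20 sham patients missed T8 and stoppers had 2, 4 or 6 more episodes than comparable stayers, the bias would be (0.20 − 0.05) × 2, 4 or 6 = 0.3, 0.6 or 0.9 episodes. Both the imbalance and the excess are invented. Both arms have the same training and visits, with a blinded sham. This is general missing-not-at-random bias, which naming T9 would not cure.
- **Early stoppers are not simply treated as completers.** Imputation conditions on their earlier values, and the training sessions are themselves assessment points. The number of sessions completed is informative only if some early stoppers have an observed T8. Otherwise its effect is extrapolated from completers.
- **Follow-up of stoppers** is retention procedure, which an article commonly leaves to the full protocol.

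What survives is narrow: the article chose its predictors, and its wording does not cover a later visit.

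**Conclusion.** The point holds in limited form. For a patient with T8 missing and T9 observed, the named predictors do not include T9, and naming it costs almost nothing. The benefit is mainly precision for the few patients with this pattern. Its size depends on the unknown T8-T9 correlation: next to nothing at 0.4, substantial at 0.7 or 0.8. Under outcome-dependent missingness T9 reduces the error of the imputed values but leaves most of it. With arm in the model, the treatment contrast moved by about 0.01 SD or less. The documents support neither a claim that T9 is ignored nor one that the primary result is biased towards verum. In a non-confirmatory pilot this is an inexpensive improvement to a stated method and does not threaten the trial's conclusions.

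**What to change.** 1. In Statistical methods, replace the sentence on preceding visits with one that admits available values from all other visits, including T9. State that T9 serves as a predictor of a missing T8 and not as its substitute, because the recall windows differ.
2. Where a patient cannot attend T8 on site, take the EDE binge count by telephone at the scheduled T8 date and flag the mode in the data. An observed count is better than an imputed one whatever the reason for absence.
3. Optionally, add the number of sessions completed to the model if some patients who stopped early have an observed T8.

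The cost is one reworded sentence, one or two more variables in the imputation model, and a short call to each patient who cannot attend T8. The downside is a small mix of on-site and telephone interviews at T8, which the flag makes visible.
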